## 5 STUDY THERAPY WITH IPILIMUMAB

### 5.1 Induction Treatment

Subjects enrolled after IC will receive ipilimumab according to the protocol of the completed Medarex study MDX010-20 (Hodi et al., NEJM, 2010) as a single agent at a dose of 3mg/kg for 4 times over 10 weeks (1 cycle): The day subjects receive the first dose of protocol ipilimumab therapy will define Day 1. Ipilimumab, 3 mg/kg, day 1 (W1), 22 (W4), 43 (W7), 64 (W10) must be administered intravenously over a 90-minute period every 3 weeks for a total of four doses, as tolerated. This dose demonstrated an overall survival benefit for the first time in treating metastatic melanoma in a controlled randomized clinical study (Hodi et al., NEJM, 2010).

- Electrocardiogram (ECG) examination should be performed during screening and week 12. Patients with an existing myocarditis are excluded from this study. For patients with suspicion of myocarditis e.g. dyspnoea, functional insufficiency etc. ECG examinations have to be performed before each treatment.
- Laboratory evaluations should be performed (refer to section 6.1.1.2) and the results examined before administration of each ipilimumab dose.
- As durable disease stabilization and/or objective tumor response can be seen after early progression before Week 12, it is recommended that, in the absence of dose-limiting toxicities (eg, serious irAEs), all four doses of ipilimumab be administered over the initial 12 weeks even in the setting of apparent clinical progression, providing the subject's performance status remains stable.
- All subjects who enter the induction period, including those who may have discontinued treatment for drug-related AEs should obtain a 12-week, 24-week 36-week and 48 week tumor assessment. Those patients who have evidence of clinical progression during the induction period, should obtain further tumor assessment according to Standard of Care.
- Based on clinical experience in the ongoing and completed melanoma studies, the following recommendations apply for subject management in light of the Week 12 or later tumor assessments:
  - The appearance of new lesions in subjects with other stable or shrinking baseline tumor burden may be experiencing clinical benefit and should continue in follow-up before alternative anti-cancer agents are considered. These subjects can be seen to have continued tumor shrinkage in follow-up scans.

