**It is necessary to skip study drug dosing for the following adverse events:**

- Any  $\geq$  Grade 3 skin related adverse event regardless of causality.

**Restart ipilimumab dosing if/when the adverse event(s) resolve(s) to  $\leq$  Grade 1 severity or returns to baseline within 2 weeks of initial dose administration:**

- If the *adverse event has resolved*, restart ipilimumab dosing at the next scheduled timepoint per protocol.
- If the adverse event has not resolved in the protocol-specified dosing window (3 weeks [ $\pm 7$  days]), the next scheduled dose will be skipped and dosing will be resumed at the subsequently scheduled dose.
- If  $> 1$  dose is expected to be skipped, the dosing schedule modifications must be discussed with the coordinating investigator prior to implementation.

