#### ***5.5.3.b Exceptions to Permanent Discontinuation***

- Potentially reversible inflammation ( $<$  Grade 4), attributable to a local anti-tumor reaction and a potential therapeutic response. This includes inflammatory reactions at sites of tumor resections or in draining lymph nodes, or at sites suspicious for, but not diagnostic of metastasis.
- Hospitalization for  $\leq$  Grade 2 adverse events where the primary reason for hospitalization is to expedite the clinical work-up.
- Patients with the following conditions where in the investigator's opinion continuing study drug administration is justified:
  - Ocular toxicity that has responded to topical therapy.
  - Endocrinopathies where clinical symptoms are controlled with appropriate hormone replacement therapy. **Note:** Ipilimumab may not be restarted while the patient is being treated with systemic corticosteroids except for patients on stable doses of hormone replacement therapy such as hydrocortisone.

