### 7.3.1 Gastrointestinal Tract

The differential diagnosis for subjects presenting with abdominal pain should include colitis, perforation, or pancreatitis. Additionally, a few subjects with abdominal pain also

had acute swelling of the cecal wall on CT scan that may have represented localized inflammation.

Diarrhea (defined as either first watery stool, or increase in frequency 50% above baseline with urgency or nocturnal bowel movement, or bloody stool) should be further

evaluated and infectious or alternate etiologies ruled out. Subjects should be advised to

inform the investigator if any diarrhea occurs, even if it is mild. An algorithm for managing subjects with diarrhea or suspected colitis is provided in Appendix 7.

The majority of subjects with ipilimumab-induced diarrhea or colitis responded to symptomatic therapy or corticosteroids. Permanent discontinuation of ipilimumab and starting high dose corticosteroid therapy (e.g., methylprednisolone 2 mg/kg once or twice per day or equivalent) is strongly recommended for ipilimumab related  $\geq$  Grade 3 diarrhea/colitis and steroids should be slowly tapered according to symptomatic response over at least 1 month.

Subjects with ipilimumab-related Grade 2 diarrhea/colitis have to skip ipilimumab dosing

and may be initially treated conservatively with loperamide, fluid replacement or budesonide, but should be immediately switched to corticosteroids (prednisone 1 mg/kg or equivalent) if symptoms persist for 3-5 days or worsen. Most subjects with diarrhea/colitis will rapidly respond to initiation of corticosteroids. The dose should be

gradually tapered over at least a 1-month duration. Lower doses of prednisone may be considered for less severe cases of colitis. It is suggested that prednisone (for oral administration) or methylprednisolone (for IV administration) be the corticosteroids of choice in the treatment of colitis. Caution should be taken in the use of narcotics in patients with abdominal pain or colitis/diarrhea as narcotic use may mask the signs of colonic perforation.

Infrequently, subjects will appear refractory to corticosteroids or will flare following taper of corticosteroids. In these subjects, unless contraindicated (i.e., sepsis, perforation and other serious infections), a single dose of infliximab at 5 mg/kg may provide benefit.

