### 7.3.3 Skin

A dermatologist should evaluate persistent or severe rash or pruritus. A biopsy should be performed if appropriate and if possible, photos of the rash should also be obtained.

Patients with low-grade ipilimumab-mediated skin toxicity (Grade 1 or 2) may remain on therapy and could be treated with symptomatic therapy (e.g., antihistamines). Low-grade symptoms persisting for 1 to 2 weeks and relapsing should be treated with topical or oral corticosteroid therapy (e.g., prednisone 1 mg/kg once daily or equivalent). High-grade (Grade 3 or 4) symptoms require high-dose IV corticosteroid therapy (e.g., methylprednisolone 2 mg/kg once or twice per day or equivalent) to control initial symptoms. A skin biopsy should be performed if appropriate. Once rash or pruritus is controlled, the initiation of corticosteroid taper should be based on clinical judgment; however, the corticosteroid dose should be gradually tapered over a period of at least 1 month.

Patients with any high-grade skin related toxicity (Grade 3 regardless of causality) have to skip ipilimumab and may only continue treatment with ipilimumab if the initial symptoms have improved to  $\leq$  Grade 1, while patients with grade 4 skin toxicities have to permanently discontinue ipilimumab.

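### The restart rule after a skipped ipilimumab dose (Section 5.5.2) is internally inconsistent on its time limit and on resolution, and the scope of the corticosteroid bar is unclear

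*Protocol*

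**What the plan says.** Section 5.5.2 (Ipilimumab Dose Skipping Rule) presents its criteria as the ones that decide skipping, restarting and discontinuing. The restart block has a lead sentence and three bullets.

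- **Lead sentence:** restart if and when the event comes down to at most "Grade 1 severity or returns to baseline within 2 weeks of initial dose administration".
- **First bullet:** if the event has resolved, "restart ipilimumab dosing at the next scheduled timepoint per protocol".
- **Second bullet:** it opens "If the adverse event has not resolved in the protocol-specified dosing window (3 weeks" (±7 days) and then states that "the next scheduled dose will be skipped and dosing will be resumed at the subsequently scheduled dose".
- **Third bullet:** if more than one skipped dose is expected, the schedule change must first be discussed with the coordinating investigator.

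Other places bear on the same decision:

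- Section 5.1: "The day subjects receive the first dose of protocol ipilimumab therapy will define Day 1", with doses on days 1, 22, 43 and 64.
- Section 5.5.3.b, in a note under the endocrinopathy exception: "Ipilimumab may not be restarted while the patient is being treated with systemic corticosteroids", with an exception for stable hormone replacement.
- Appendix 10-15, 7.3.1: Grade 2 diarrhea/colitis leads to a skipped dose. If symptoms persist for 3-5 days or worsen, corticosteroids are started and then "gradually tapered over at least a 1-month duration".
- Appendix 10-15, 7.3.3: a patient with a Grade 3 skin event may continue only after improvement to Grade 1 or less.

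**The concern.** The restart block governs doses 2 to 4. It also governs the same doses in every re-induction, because Section 5.2 repeats the treatment phase. A site that follows the lead sentence literally would end treatment after any event that starts beyond day 15. A site that follows the second bullet literally would give the dose after a skip whether or not the event had resolved. A site that reads only Section 5.5.2 would not see the corticosteroid note at all.

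With up to 26 sites (synopsis), the number of doses a patient receives after a toxicity could depend on which sentence the site applies. That is first a safety matter. It also blurs what treatment was given, and so the reading of the secondary endpoint of related adverse events of Grade 3 or higher.

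**Working it through.** The plan gives no figure to reproduce. The check is a day count and a side-by-side reading.

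**Inputs.** Dose days 1, 22, 43, 64 and Day 1 = first dose (Section 5.1); 2-week limit and window of 3 weeks ±7 days (Section 5.5.2); taper of at least 1 month (Appendix 10-15, 7.3.1). I take a month as 28 to 31 days (assumption).

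**1. The time limit, under three readings.**

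| Reading of the 2 weeks | Limit | Against the bullets |
|---|---|---|
| From the first dose | 1 + 14 = day 15 | Ends before days 22, 43 and 64. An event resolving on day 18 fails the lead sentence but is due on day 22 under the first bullet. An event starting on day 16 or later can never qualify. |
| From the preceding dose | 14 days after that dose | The window is 21 − 7 = 14 to 21 + 7 = 28 days. Resolution 15 to 28 days after the dose fails the lead sentence but lies inside the window. |
| Qualifies only the return to baseline | None for resolution to Grade 1 | The clash remains only where baseline itself was above Grade 1, since otherwise the Grade 1 condition applies without a time limit. |

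The first reading also sits badly with the protocol's own background: Section 1.3.5 puts the first onset of endocrine events typically at weeks 6 to 12, all after day 15.

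**2. Resolution.** Take an event after dose 1 that is still above Grade 1 on day 22 + 7 = day 29, and again on day 43. The second bullet skips day 22 and resumes on day 43, with no condition attached. The lead sentence is not met on day 43. For a Grade 3 skin event, Appendix 10-15, 7.3.3 also bars that dose. The third bullet applies only when more than one skip is expected, and a site applying the second bullet as written expects one. This conflict does not depend on how the 2 weeks is read.

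**3. Corticosteroids, if the note in Section 5.5.3.b is general.** Let *s* be the day steroids start, and count the taper from *s*, the shortest course the text allows. The patient is on steroids on day 43 if *s* ≤ 43 < *s* + 28, so *s* runs from 16 to 43. With a 31-day month, *s* runs from 13 to 43.

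- *s* = 20: steroids run to about 20 + 28 = day 48. If the event followed dose 1 and day 22 was skipped, the second bullet schedules day 43 and the note bars it.
- *s* after a dose given on day 22: the first bullet schedules day 43 if the event has resolved on treatment by then, and the note bars it. If it has not resolved, the second bullet skips day 43 and points to day 64.
- *s* = 8: steroids can end at 8 + 28 = day 36, and day 43 is free.

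The clash at day 43 is therefore possible over a range of start days and is not universal.

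**The case against.** The strongest reply is that the block should be read as a whole. All three bullets stand under a lead sentence that makes resolution the condition for restart, so the second bullet may only set timing. The third bullet then brings in the coordinating investigator for a patient who is still unresolved at the following dose. Section 5.5.2 also asks the investigator to contact the PI about any event that prompts a skip, and it allows skipping on clinical judgment. This is a reasonable reading, and it reduces the practical risk. It does not remove the conflict: the second bullet is addressed to unresolved events and says without qualification that dosing resumes. The third bullet helps only a site that already reads the lead sentence as prevailing.

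A second reply is that the corticosteroid note adds a condition and contradicts nothing, since a site can satisfy both sections by waiting. That stands in part. The note can be read as cumulative, or as confined to endocrinopathy, where it is printed. What remains is that Section 5.5.2 neither mentions nor cross-refers to it, so its scope is undefined.

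A reader might infer more than the documents support:

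- **That the two sections collide in every steroid-treated event.** They do not. Early courses can end before the next dose, stable hormone replacement is exempt, and most related non-skin events of Grade 3 or higher require permanent discontinuation under Section 5.5.3.a, so restart does not arise.
- **That low-grade skin events are a further example.** Appendix 10-15, 7.3.3 says "Patients with low-grade ipilimumab-mediated skin toxicity (Grade 1 or 2) may remain on therapy", and Section 5.5.2 makes a skip necessary for skin events only from Grade 3. Such patients would not normally have skipped, so there is nothing to restart.
- **That patients admitted on a fixed steroid dose for brain metastases face a contradiction, or that results in that subgroup are distorted.** Eligibility on steroids and a stricter condition after a skip can coexist. The text leaves their position unstated, and nothing links it to the subgroup results.

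**Conclusion.** The restart block in Section 5.5.2 is inconsistent as written. The time limit fails on a literal reading (day 15) and does not fit the dosing window when counted from the preceding dose (14 days against 14 to 28). It weakens if the 2 weeks attaches only to the return to baseline. The missing resolution condition in the second bullet stands on every reading of the time limit. The corticosteroid point is one of unclear scope. It becomes a direct clash at day 43, for steroid starts between about day 16 and day 43 (day 13 with a 31-day month), only if the note is general and Section 5.5.2 schedules that dose.

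The number of patients affected is unknown. A reader might scale the 3 mg/kg rates in Table 3 of Section 1.3.5.b (64.8% with any irAE, 32.4% gastrointestinal) to 200 patients. Those are any-grade rates: they include Grade 1 events and, in the overall rate, skin events that mostly would not trigger a skip. The study behind them also gave maintenance doses.

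The definition of the primary endpoint and the sample size are not touched. The case for correcting the text is safety and uniform dosing across sites.

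**What to change.** Reconcile the restart block of Section 5.5.2, the note in Section 5.5.3.b, and 7.3.1 and 7.3.3 of Appendix 10-15 into one restart rule that states:

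- a single time limit with one named anchor, if a limit is intended, consistent with the dosing window and usable for events after any dose and in re-induction;
- whether resolution is required before the dose that follows a skipped dose, written into the second bullet;
- the scope of the corticosteroid note: endocrinopathy only or all events, and whether it covers patients admitted on fixed-dose steroids for brain metastases, with a cross-reference from Section 5.5.2.

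Which clinical conditions apply is for the sponsor to decide. The cost is amendment wording and a letter to sites, with no added patients or procedures.

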### 5.5.3 Discontinuation of Study Therapy

Subjects MUST be discontinued from study therapy AND/ OR withdrawn from the study for the following reasons:

- Withdrawal of informed consent (subject's decision to withdraw for any reason)
- Any clinical adverse event, laboratory abnormality or intercurrent illness which, in the opinion of the investigator, indicates that continued treatment with study therapy is not in the best interest of the subject
- Clinical deterioration of subject's condition such that further benefit from ipilimumab dosing is unlikely or requires a change of therapy
- The development of progression (PD) in the global tumor burden (progression must be confirmed by serial imaging 4-6 weeks later)
- Pregnancy
  - All WOCBP should be instructed to contact the investigator immediately if they suspect they might be pregnant (e.g., missed or late menstrual period) at any time during study participation. Institutional policy and local regulations should determine the frequency of on study pregnancy tests for WOCBP enrolled in the study.
  - The investigator must immediately notify the coordinating investigator in the event of a confirmed pregnancy in a patient participating in the study.
- Termination of the study
- The compulsory detention for treatment of either a psychiatric or physical (e.g., infectious disease) illness

If study drug administration is discontinued, the reason for discontinuation will be recorded.

#### 5.5.3.a *Permanent Discontinuation for Related Adverse Events*

**The following treatment related non-neurological adverse events require permanent discontinuation of ipilimumab:**

- Any  $\geq$  Grade 2 eye pain or reduction of visual acuity that does not respond to topical therapy and does not improve to  $\leq$  Grade 1 severity within 2 weeks of starting therapy, OR, requires systemic treatment.
- Any  $\geq$  Grade 3 bronchospasm or other hypersensitivity reaction.
- Any other  $\geq$  Grade 3 non-skin related adverse event with the exception of events listed under "No Discontinuation" (below).
  - Any  $\geq$  Grade 4 laboratory abnormalities, except AST, ALT, or Total Bilirubin
  - AST or ALT  $> 8 \times$  ULN
  - Total Bilirubin  $> 5 \times$  ULN
  - Any other  $\geq$  Grade 4 adverse event

- Any adverse event, laboratory abnormality or intercurrent illness which, in the judgment of the investigator, presents a substantial clinical risk to the patient with continued dosing.

Please refer to the IB for specific treatment algorithms.

**The following neurological adverse event requires permanent discontinuation of ipilimumab and defines unacceptable neurotoxicity:**

- Any motor neurologic toxicity  $\geq$  Grade 3 regardless of causality
- Any  $\geq$  Grade 3 treatment related sensory neurologic toxicity

Please refer to the IB for specific treatment algorithms.

#### ***5.5.3.b Exceptions to Permanent Discontinuation***

- Potentially reversible inflammation ( $<$  Grade 4), attributable to a local anti-tumor reaction and a potential therapeutic response. This includes inflammatory reactions at sites of tumor resections or in draining lymph nodes, or at sites suspicious for, but not diagnostic of metastasis.
- Hospitalization for  $\leq$  Grade 2 adverse events where the primary reason for hospitalization is to expedite the clinical work-up.
- Patients with the following conditions where in the investigator's opinion continuing study drug administration is justified:
  - Ocular toxicity that has responded to topical therapy.
  - Endocrinopathies where clinical symptoms are controlled with appropriate hormone replacement therapy. **Note:** Ipilimumab may not be restarted while the patient is being treated with systemic corticosteroids except for patients on stable doses of hormone replacement therapy such as hydrocortisone.

#### **5.5.4 Immune-Related Adverse Events (irAEs): Definition, Monitoring, and Treatment**

Blocking CTLA-4 function may permit the emergence of auto-reactive T cells and resultant clinical autoimmunity. Rash/vitiligo, diarrhea/colitis, uveitis/episcleritis, hepatitis, and hypopituitarism were drug-related, presumptive autoimmune events, now termed irAEs, noted in previous ipilimumab studies.

For the purposes of this study, an irAE is defined as an AE of unknown etiology associated with drug exposure and consistent with an immune phenomenon. Efforts should be made to rule out neoplastic, infectious, metabolic, toxin or other etiologic causes prior to labeling an AE an irAE. Serological, immunological, and histological (biopsy) data should be used to support

the diagnosis of an immune-mediated toxicity. Suspected irAEs must be documented on an AE or SAE form.

Patients should be informed of and carefully monitored for evidence of clinically significant systemic irAE (e.g., systemic lupus erythematosus-like diseases) or organ-specific irAE (e.g., rash, colitis, uveitis, hepatitis or thyroid disease). If an irAE is noted, appropriate work-up (including biopsy if possible) should be performed, and steroid therapy may be considered if clinically necessary.

It is unknown if systemic corticosteroid therapy has an attenuating effect on ipilimumab activity. However, clinical anti-tumor responses have been maintained in patients treated with corticosteroids and discontinued from ipilimumab. If utilized, corticosteroid therapy should be individualized for each patient. Prior experience suggests that colitis manifested as  $\geq$  Grade 3 diarrhea requires corticosteroid treatment.

Specific treatment algorithms for immune-related adverse events are included as appendices in the IB.

### 5.5.5 Other Guidance

#### **5.5.5.a Treatment of Infusion Reactions Associated with Ipilimumab**

Since ipilimumab contains only human protein sequences, it is less likely that any allergic reaction will be seen in patients. However, it is possible that infusion of ipilimumab will induce a cytokine release syndrome that could be evidenced by fever, chills, rigors, rash, pruritus, hypotension, hypertension, bronchospasm, or other symptoms. No prophylactic pre-medication will be given unless indicated by previous experience in an individual patient. Reactions should be treated based upon the following recommendations.

- For mild symptoms (e.g., localized cutaneous reactions such as mild pruritus, flushing, rash):
  - Decrease the rate of infusion until recovery from symptoms, remain at bedside and monitor patient.
  - Complete the ipilimumab infusion at the initial planned rate.
  - Diphenhydramine 50 mg IV may be administered at the discretion of the treating physician and patients may receive additional doses with close monitoring.
  - Premedication with diphenhydramine may be given at the discretion of the investigator for subsequent doses of ipilimumab.
- For moderate symptoms (any symptom not listed above [mild symptoms] or below [severe symptoms] such as generalized pruritus, flushing, rash, dyspnea, hypotension with systolic BP  $>80$  mmHg):
  - Interrupt ipilimumab.

- Administer diphenhydramine 50 mg IV.
- Monitor patient closely until resolution of symptoms.
- Corticosteroids may abrogate any beneficial immunologic effect, but may be administered at the discretion of the treating physician.
- Resume ipilimumab infusion after recovery of symptoms.
- At the discretion of the treating physician, ipilimumab infusion may be resumed at one half the initial infusion rate, then increased incrementally to the initial infusion rate.
- If symptoms develop after resumption of the infusion, the infusion should be discontinued and no additional ipilimumab should be administered that day.
- The next dose of ipilimumab will be administered at its next scheduled time and may be given with pre-medication (diphenhydramine and acetaminophen) and careful monitoring, following the same treatment guidelines outlined above.
- At the discretion of the treating physician additional oral or IV antihistamine may be administered prior to dosing with ipilimumab.
- For severe symptoms (e.g., any reaction such as bronchospasm, generalized urticaria, systolic blood pressure <80 mm Hg, or angioedema):
  - Immediately discontinue infusion of ipilimumab, and disconnect infusion tubing from the subject.
  - Consider bronchodilators, epinephrine 1 mg IV or subcutaneously, and/or diphenhydramine 50 mg IV, with solumedrol 100 mg IV, as needed.
  - Patients should be monitored until the investigator is comfortable that the symptoms will not recur.
  - No further ipilimumab will be administered.
- In case of late-occurring hypersensitivity symptoms (e.g., appearance within one week after treatment of a localized or generalized pruritus), symptomatic treatment may be given (e.g., oral antihistamine, or corticosteroids).

